### Secondary outcome

#### Clinical outcome

Time to clinical improvement (TTCI) [time frame: up to 28 days]
A.Time to clinical improvement (TTCI) was defined as time from randomization to a decline of 2 categories on the seven-category ordinal scale of clinical status or live discharge from the hospital, whichever came firstClinical status assessed by 7-category ordinal scale on days 7, 14, and 28Change in National Early Warning Score (NEWS) from baseline to day 28 [time frame: day 1 through day 28]*The NEW score has demonstrated an ability to discriminate patients at risk of poor outcomes. This score is based on 7 clinical parameters (respiration rate, oxygen saturation, any supplemental oxygen, temperature, systolic blood pressure, heart rate, level of consciousness). The NEW Score is being used as an efficacy measureTime to National Early Warning Score (NEWS) of ≤ 2 and maintained for 24h 28 [time frame: day 1 through day 28]Duration of hospitalization [time frame: day 1 through day 28] measured in daysDuration of new non-invasive ventilation or high flow oxygen use [time frame: day 1 through day 28]Incidence of new non-invasive ventilation or high flow oxygen use [time frame: day 1 through day 28]Duration of new supplement oxygen use [time frame: day 1 through day 28]Incidence of new supplement oxygen use [time frame: day 1 through day 28]Duration of new ventilator or extracorporeal membrane oxygenation (ECMO) use [time frame: day 1 through day 28]Incidence of new ventilator or extracorporeal membrane oxygenation (ECMO) use [time frame: day 1 through day 28]Mortality at day 28 [time frame: day 1 through day 28]. Date and cause of death (if applicable)Time (days) from treatment initiation to death

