#### Virological endpoints

1. Proportions of patients with a negative nasopharyngeal swab and sputum sample for SARS-CoV-2 quantitative RT-PCR on days 3, 7, 10, 14, and 21 after starting treatment

2. Viral load change (log10 viral load) of nasopharyngeal swab and sputum sample for SARS-CoV-2 quantitative RT-PCR on days 3, 7, 10, 14, and 21 after starting treatment

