**ASSESSMENTS:**									
*[SARS-CoV RT-PCR]*	X			X	X	X	X		
*[Chest X-ray]*	X			X	X	X	X		
*[Chest CT]*	X						X		
*[Physical examination]*	X								
*[Viral signs]*	X		X	X	X	X	X	X	X
*[Symptoms]*	X		X	X	X	X	X	X	X
*[Seven category ordinary scale]*	X		X	X	X	X	X	X	X
*[NEWS score]*	X				X		X	X	X
*[Blood test]*	X		X	X	X	X	X	X	X
*[Blood collection for research]*			X		X				
*[Adverse reaction]*			X	X	X	X	X	X	X

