### Plans for communicating important protocol amendments to relevant parties (e.g., trial participants, ethical committees) {25}

In April 2020, version 2.0, which is initial version of the trial protocol, was submitted to the Ministry of Food and Drug Safety in Korea (MFDS). MFDS approval was granted on April 17 2020. In May 2020, an amendment (version 3.0) was submitted to the MFDS. Protocol changes in this amendment included the following: the contents of patients without standard treatment (e.g., emergency) were revised by referring to the definition of vulnerable subjects in the clinical trial management criteria, addition of serious adverse events (including LFT abnormalities) to the discontinuation criteria, NEWS (National Early Warning Score) added in clinical data collection, revision of the definition of adverse events and actions to be taken in the event of an adverse reaction, and addition of information regarding the storage institution and disposal method of the consent form for human materials. MFDS approved version 3.0 on May 28, 2020. In June 2020, a minor amendment (version 3.1) was submitted to the MFDS. Protocol changes in this amendment included the following: change schedule in the confirmation of virological endpoints through SARS-CoV-2 quantitative RT-PCR. MFDS approved version 3.1 on June 11, 2020. Patient recruitment commenced in April 2020, and the last patient will be recruited to the trial in April 2021. The last visit of the last patient is anticipated to occur in April 2021.

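### The printed assessment schedule does not support the secondary endpoint of NEWS of 2 or less held for 24 hours, and has no RT-PCR sample for the day-21 time point of the two virological endpoints

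*Protocol article*

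**What the plan says.** **NEWS.** Under Secondary outcome, Clinical outcome, the protocol article defines a time-to-event endpoint: NEWS of 2 or less, "maintained for 24h 28 [time frame: day 1 through day 28"]. The 28 directly after 24h looks like a stray character, so I read the condition as 24 hours. The same section describes the score: "This score is based on 7 clinical parameters (respiration rate, oxygen saturation, any supplemental oxygen, temperature, systolic blood pressure, heart rate, level of consciousness"). In the Participant timeline {13}, the NEWS row is marked at screening, D7, D14, D21 and D28.

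**Virology.** Under Virological endpoints there are two items: the proportion of patients with negative samples, and "Viral load change (log10 viral load) of nasopharyngeal swab and sputum sample". Each is to be evaluated "on days 3, 7, 10, 14, and 21 after starting treatment". In the timeline, the row labelled "SARS-CoV RT-PCR" is marked at screening, D3, D7, D10 and D14. The D21 and D28 cells are blank.

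**Amendment history.** The section on communicating amendments {25} reports that version 3.1 brought a "change schedule in the confirmation of virological endpoints through SARS-CoV-2 quantitative RT-PCR". It does not give the old or the new days. Trial status names 3.1 as the current version.

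**The concern.** Showing that a score has been held for 24 hours takes at least two scores spanning 24 hours. With weekly scores, a single value of 2 or less says nothing about the day before or after it. A value above 2 does not rule out a qualifying 24-hour spell since the previous visit. Patients who recover on day 2 and on day 6 would look the same. A trial of 84 patients that looks for faster recovery would lose most of what this endpoint could show.

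The RT-PCR mismatch is a plain disagreement between two current parts of the document. A site that follows the timeline takes no day-21 sample; a site that follows the endpoint list does. With 10 hospitals, day-21 data could end up partial, with availability depending on the site.

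**Working it through.** No sample size, power or error rate enters this point. The check sets the days that each endpoint needs against the days that the timeline provides. The timeline has nine columns (-D1, D0, D1, D3, D7, D10, D14, D21, D28). The three rows used here each have nine cells, so the marks line up without ambiguity. The row printed as viral signs I read as vital signs.

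| Row | Days marked | Gaps between consecutive marked days |
|---|---|---|
| NEWS | -1, 7, 14, 21, 28 | 8, 7, 7, 7 |
| Vital signs (after baseline) | 1, 3, 7, 10, 14, 21, 28 | 2, 4, 3, 4, 7, 7 |
| RT-PCR | -1, 3, 7, 10, 14 | 4, 4, 3, 4 |

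**Step 1: NEWS as scheduled.** The gaps are 7 − (−1) = 8, then 14 − 7 = 7, 21 − 14 = 7 and 28 − 21 = 7 days. The smallest is 7 days, against the 1 day required. None of the 4 post-baseline scores has a partner 24 hours away. The only recovery times that can be recorded are 7, 14, 21 and 28 days.

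**Step 2: NEWS rebuilt from other visits.** Suppose all seven parameters were available at every vital-sign visit, which the article does not say. The post-baseline gaps would be 3 − 1 = 2, 7 − 3 = 4, 10 − 7 = 3, 14 − 10 = 4, 21 − 14 = 7 and 28 − 21 = 7 days. The smallest is 2 days, so 24-hour maintenance still cannot be confirmed.

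**Step 3: RT-PCR.** Days needed: {3, 7, 10, 14, 21}. Post-baseline days scheduled: {3, 7, 10, 14}. The difference is {21}, so 1 of 5 time points (20%) has no scheduled sample, for both virological endpoints. The vital-sign, symptom, ordinal-scale and NEWS rows all carry a mark at D21, so the blank is specific to RT-PCR and is not a lost column.

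**Step 4: what is not affected.** The change in NEWS from baseline to day 28 has both of its scores. The virus removal rate on day 14, the one virological analysis singled out under Statistical methods {20a}, has its sample. The ordinal scale behind the primary outcome is marked at D14 and D28.

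**The case against.** The best reply is that the timeline is not the whole data-capture plan. The secondary outcomes include durations of hospitalization, oxygen use and ventilation, and none of these has a row in it. The section on outcome collection {18a} also has the clinician evaluating NEWS and treatment progress during hospitalization. The article condenses a full protocol that is not shown, and more frequent in-hospital scoring may be specified there. This limits the claim: the printed schedule does not support the endpoint, but that does not prove the data will never exist. It does not remove the conflict, because the article gives NEWS an explicit row of days and those days do not fit the definition. Section {18a} states no more frequent scoring.

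A second reply is that the RT-PCR mismatch may only be an incomplete update at version 3.1. That is plausible, but both lists are current text and the article does not say which one governs.

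A reader might also infer more than the document supports:

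- *The virological endpoints cannot be delivered.* Four of their five time points are sampled.
- *Day-21 virology would be filled in with a mean or median under the missing-data section {20c}.* If no one is sampled on day 21, there is no observed day-21 value from which to take a mean or median. Nothing in that section says it covers assessments that were never scheduled.
- *The wide late gaps in the ordinal scale undermine time to clinical improvement in the same way.* That endpoint also counts live discharge, which has its own date. A two-category decline from category 3 or 4 reaches category 1 or 2, both of which already mean out of hospital. Visit spacing could therefore matter only for patients who start in category 5 or 6.

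**Conclusion.** The point holds in two parts, both confined to secondary outcomes.

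(a) On the printed schedule, time to NEWS of 2 or less held for 24 hours cannot be determined as defined. No pair of scheduled scores is 24 hours apart, and the timing is resolved only to about 7 days over a 28-day window.

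(b) The endpoint list and the timeline disagree on RT-PCR at day 21, which leaves 1 of 5 time points without a scheduled sample for both virological endpoints.

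Part (a) is the more serious, because an analysis plan can settle derivations but cannot supply readings that sites were not asked to take. Part (b) is an inconsistency to be reconciled. Both parts assume that the timeline is what sites follow for NEWS and RT-PCR, and part (a) also reads the 24h condition literally.

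**What to change.** **NEWS, one of two routes.**

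1. Keep the definition and record NEWS at least daily during admission, from ward observations where all seven parameters are charted. The cost is extra data entry. There would be no such data after discharge, so the plan must say how discharged patients are handled. Counting discharge itself as NEWS of 2 or less is not a neutral way to do this: it adds a new event to a physiological endpoint and makes it overlap with time to clinical improvement.
2. Keep the present visits and redefine the endpoint as the first scheduled visit with NEWS of 2 or less. Drop the 24-hour condition and analyse the time as interval-censored between visits. This costs only a change of wording and method, but timing stays coarse at about a week.

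In either case, remove the stray 28 from the definition.

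**RT-PCR.** Reconcile the Virological endpoints section with the RT-PCR row of the timeline so that both name the same days, and tell all sites which list applies. The document does not show which list is intended, so the sponsor must decide. The edit itself costs nothing; any sampling cost depends on that decision.

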## Eligibility criteria {10}

### Inclusion criteria

18 years old or olderPatients who have been confirmed of COVID-19 infection and has evidence for pneumonia
A.Confirmation of COVID-19 infection by RT-PCR of SARS-CoV-2B.Definite diagnosis of new infiltration of the lungs by chest CT scan of chest radiographic inspection3.Patients who are within 72 h of COVID-19 pneumonia confirmation4.Patients with 3 (hospitalization, not requiring supplemental oxygen) or higher in seven-category ordinal scale of clinical status5.Patients who are eligible for diagnosis/evaluation to chest CT scan and related to it6.Patients should be able to understand the essence of the clinical trial and to submit a written consent document. For the patients who can understand the nature of the research but cannot sign the document, a relative can agree to the study.

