## Outcomes {12}

### Primary outcome

The primary outcome is as follows: proportion of patients with clinical improvement as defined by live discharge from hospital or a decline of 2 categories on the seven-category ordinal scale of clinical status [time frame: day 14 and day 28]

*Seven-category ordinal scale of clinical status
Not hospitalized with resumption of normal activities;Not hospitalized, but unable to resume normal activities;Hospitalization, not requiring supplemental oxygen;Hospitalization, requiring supplemental oxygen;Hospitalization, requiring nasal high-flow oxygen therapy and/or noninvasive mechanical ventilation;Hospitalization, requiring extracorporeal membrane oxygenation and/or invasive mechanical ventilation;Death.

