## Statistical methods

### Statistical methods for primary and secondary outcomes {20a}

Intention-to-treat analysis and per protocol analysis will be conducted respectively, and intention-to-treat analysis will be performed as the main analysis.The categorical variable of the evaluation index will be analyzed using Pearson’s chi-square test, and the continuous variable will be analyzed using ANOVA or Kruskal–Wallis test.The virus removal rate on day 14, one of the secondary outcomes, will be analyzed using Pearson’s chi-square test.Time to clinical improvement will be assessed on all subjects by day 28. If there is no clinical improvement or a case of death by day 28, it will be recorded as day 28, and analyzed by Kaplan–Meier plot and log-rank test.

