## Methods in analysis to handle protocol non-adherence and any statistical methods to handle missing data {20c}

Outcome data obtained from all randomized participants will be included in the main analyses to prevent attrition bias. To prevent missing data, the researcher, trained research nurse, and research assist will double check the data as well as the recording of reasons for missing data. By replacing missing data with the mean or median value, we plan to analyze with minimal data loss.

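### Four secondary endpoints are plain durations with no rule for death or escalation, so early failure can score as a shorter, apparently better result

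*Protocol article*

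**What the plan says.** The protocol article lists four durations under Secondary outcome, Clinical outcome, each over days 1 to 28:

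- hospital stay, counted in days;
- "Duration of new supplement oxygen use [time frame: day 1 through day 28"];
- new NIV or high-flow oxygen use;
- "Duration of new ventilator or extracorporeal membrane oxygenation (ECMO) use [time frame: day 1 through day 28"].

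None is worded as support-free days or as days alive and out of hospital. Mortality is a separate item: "Mortality at day 28 [time frame: day 1 through day 28]. Date and cause of death (if applicable"). Each type of support also has its own incidence endpoint.

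Under Statistical methods {20a}, "the continuous variable will be analyzed using ANOVA or Kruskal–Wallis test". The same section has one rule that mentions death, and it belongs to time to clinical improvement: "If there is no clinical improvement or a case of death by day 28, it will be recorded as day 28". The missing-data section {20c} adds only this: "By replacing missing data with the mean or median value, we plan to analyze with minimal data loss". It does not mention death or a change in the level of support.

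**The concern.** A duration of use is a good measure only if a short value means recovery. In these patients it can also mean death, or failure of one level of support and a move to the next. Death stops the count of ventilator, oxygen and hospital days. Intubation stops the count of NIV/high-flow days, because the ordinal scale treats "Hospitalization, requiring nasal high-flow oxygen therapy and/or noninvasive mechanical ventilation" as a category separate from invasive ventilation and ECMO, and the two have separate duration endpoints.

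Deaths are plausible in this population. Entry is open to "Patients with 3 (hospitalization, not requiring supplemental oxygen) or higher in seven-category ordinal scale of clinical status" with no upper limit short of death, and the only related exclusion is for patients judged likely to die within 3 days of randomisation. The abstract hopes that nafamostat lowers mortality, so the treatment may change the very event that distorts these endpoints. At stake are four secondary comparisons, one of which (hospital stay) is named in the abstract and in the secondary objective.

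**Working it through.** The protocol gives no figure for these endpoints, so there is none to reproduce. The check has two parts.

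**1. Endpoint against analysis rule.** The durations are day counts. The continuous-variable rule sends day counts to ANOVA or Kruskal–Wallis. The rule that records death as day 28 is tied to time to clinical improvement. Followed as written, a patient ventilated on day 3 who dies on day 6 contributes 3 ventilator days, and one who recovers after 12 ventilator days contributes 12.

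**2. Illustration.** From the protocol: 42 patients per arm (Sample size) and a 28-day window. Everything else is assumed: 6 per arm are newly ventilated, and the other 36 are never ventilated and alive at day 28. On control, 3 die after 3 ventilator days and 3 recover after 14. On nafamostat, 1 dies after 3 days and 5 recover after 12. Patients without ventilation count as 0 days.

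Mean raw ventilator days = total days / 42:
- control: (3×3 + 3×14)/42 = 51/42 = 1.21
- nafamostat: (1×3 + 5×12)/42 = 63/42 = 1.50

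Mean ventilator-free days, with 28 minus ventilator days for survivors and 0 for deaths:
- control: (36×28 + 3×14 + 3×0)/42 = 1050/42 = 25.0
- nafamostat: (36×28 + 5×16 + 1×0)/42 = 1088/42 = 25.9

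On raw days nafamostat looks 0.29 day worse, although it has fewer deaths and its survivors wean sooner. On free days it is 0.9 day better.

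**Ranks.** The reversal above is in means, so it bears on ANOVA. For Kruskal–Wallis, compare each ventilated nafamostat patient with each ventilated control patient (6×6 = 36 pairs). Pairs involving never-ventilated patients tie or cancel. On raw days nafamostat is longer in 5×3 = 15 pairs, shorter in 5×3 + 1×3 = 18, and tied in 3. On free days it is better in 5×6 = 30, worse in 1×3 = 3, and tied in 3. Here ranks do not reverse, but most of the real advantage is lost.

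Ranks do mislead when survivors wean at the same time. Suppose all survivors are ventilated 14 days and deaths come after 3, with 0 deaths in one arm and 3 in the other. The arm without deaths has longer raw duration in 6×3 = 18 pairs and shorter in none. Raw means are 84/42 = 2.00 against 51/42 = 1.21. Free days are (36×28 + 6×14)/42 = 26.0 against 25.0.

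**Hospital stay** (assumed: survivors stay 16 days, deaths on day 6, 2 against 6 deaths). Raw means are (40×16 + 2×6)/42 = 15.5 and (36×16 + 6×6)/42 = 14.6 days, so the arm with more deaths looks better. Days alive and out of hospital, with death = 0, are 40×12/42 = 11.4 and 36×12/42 = 10.3, so the order reverses. With 1 against 2 deaths the raw shift is only (16−6)/42 = 0.24 day.

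**NIV/high-flow** (assumed: 6 users per arm; all use it for 8 days in one arm, while 3 of 6 are intubated after 2 days in the other). Means over all 42 are 48/42 = 1.14 and (3×8 + 3×2)/42 = 0.71 days. The arm with the intubations has the shorter duration.

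**The case against.** The strongest reply is that this rests on silence. The article condenses a longer protocol, and the handling of death or of patients with no use in a secondary duration is often left to that document or to the analysis plan. An unseen plan could add a rule. What stands is that the current text does not rule out a correction. But the objection is to the endpoint that was chosen, not to missing detail: days of use are named as the outcome and a test is given for continuous variables. Scoring death as worst would change that endpoint.

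The second reply is that other outcomes protect the reader, and this is largely right. The primary outcome counts only live discharge or a two-category decline. The incidence endpoints address need for support, and the ordinal scale on days 7, 14 and 28 ranks death as worst. A reader might therefore infer that the trial cannot tell whether nafamostat reduces need for support, or that a harmful drug would come out looking good overall. The documents support neither inference. The other outcomes would expose the harm; they do not repair the duration comparisons.

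Three further inferences go too far:

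- That durations exist only for patients who used the support. The text does not say whether non-users count as 0 or are left out. Leaving them out would compare groups selected after randomisation.
- That patients ventilated at entry drive the ventilator endpoint. It concerns new use. Those patients bear on hospital stay and mortality.
- That escalation from high-flow shortens ventilator/ECMO duration. It does not. It shortens NIV/high-flow duration, and oxygen duration if ventilator days are not counted there.

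**Conclusion.** The concern holds for the four duration endpoints. As written, early death shortens all of them and intubation shortens NIV/high-flow duration, so the comparisons can favour the arm with more early failures.

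The size is modest. In the illustration the mean moves 0.29 day in the wrong direction, where free days show 0.9 day in the right one. Restricting the same inputs to the 6 ventilated patients per arm gives far larger gaps (8.5 against 10.5 raw days; 7.0 against 13.3 free days). Those figures should not be read as the likely effect, because the sound comparison covers all 42 per arm.

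All death counts and day counts are assumptions. The distortion needs deaths that come before support or stay would otherwise have ended: a late death after long support gives a long duration, and with few deaths the effect is small. The Kruskal–Wallis option reduces the problem for some patterns and not for others. The primary outcome is not affected. The change should be made, but it does not threaten the main conclusion.

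**What to change.** For the between-arm comparison, replace the four durations with:

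- days alive and free of supplemental oxygen or any higher support, through day 28;
- days alive and free of NIV/high-flow or any higher support;
- days alive and free of ventilator/ECMO;
- days alive and out of hospital.

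Score patients who die by day 28 as 0, compute each over all randomised patients, and compare by a rank test. Counting the given level or higher means that intubation no longer ends the unfavourable period. Never-users then have a defined value, which settles the open question about them. Keep the raw durations as descriptive only, and show mortality beside each composite.

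Cost: date of death is already listed as an outcome. Start and stop dates are implied by the duration endpoints, although the schedule of assessments does not list them, so their collection should be confirmed. Because the trial is registered and already enrolling, changing secondary endpoints needs a protocol and registry amendment. The composite also mixes death with support, so it cannot be interpreted without the mortality result next to it.
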